### Statistical analyses

#### Effect evaluation

Descriptive variables, primary and secondary outcome measures at baseline and after six months will be presented for the two guidance strategies per construction company using descriptive statistics. Differences in descriptive variables between the two guidance strategies will be tested using an independent samples *t*-test for continuous data or a Chi-square test for proportions.

The results of the primary and secondary outcome measures on the individual worker level may be influenced by the dependency of the company in which an individual worker is working. To correct for this dependency, the statistical analyses of the outcome measures to test differences between baseline and after six months for both guidance strategies will be done using a Generalized Linear Mixed Model. IBM SPSS Statistics 20 will be used for the statistical tests.

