Within the review of van Eerd *et al*. [16], fifteen out of 16 studies found that the presence of a PE specialist, defined as an ergonomics consultant, was a facilitator to the PE intervention process. The role of this ergonomics consultant was firstly to initiate and then to guide the PE intervention process [16]. In this study, we want to investigate the effect of two types of guidance strategies on the use of ergonomic measures, as well as on health outcomes. In addition, we want to evaluate the process and the costs-benefits of both guidance strategies. The two guidance strategies are: 1) a face-to-face guidance strategy in which the ergonomics consultant guides the PE intervention through face-to-face contacts with the PE team; and 2) an e-guidance strategy in which the ergonomics consultant guides the PE intervention by means of e-mail contacts with the PE team.

We hypothesise that the face-to-face guidance strategy will increase the use of ergonomic measures, work ability, and physical functioning while decreasing limitations due to physical problems more when compared to the e-guidance strategy. This would be due to a higher compliance to the face-to-face guidance strategy compared with the e-guidance strategy, as a result of the presence of the ergonomics consultant within the face-to-face guidance strategy. Although the financial costs will be higher in the face-to-face guidance strategy, due to more time spent by the ergonomics consultant during the guidance sessions, more financial benefits will be gained through reduced physical risk factors due to an increase in the use of ergonomic measures.

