### Study design

A randomised intervention trial with a follow-up at six months is performed to compare the effectiveness of the two ergonomic guidance strategies, a face-to-face guidance strategy and an e-guidance strategy, of a PE intervention. The effectiveness of both guidance strategies will be compared on the use of ergonomic measures, work ability, physical functioning, limitations due to physical problems of individual construction workers, a process evaluation and a cost-benefit evaluation.

According to the researchers, the study protocol did not met the criteria of the “Act medical-scientific research with human participants” and therefore, the Medical Ethics Committee of the Academic Medical Center Amsterdam (AMC) was not asked for approval of the study protocol.

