### Sample size

The sample size is based on detecting a difference in the use of a new ergonomic measure between the face-to-face guidance strategy and the e-guidance strategy. In a study of Jensen and Friche [6], it was found that daily use of new introduced construction working methods could be at least 10%. We have decided that a 15% absolute difference in use of newly introduced ergonomic measures between the two guidance strategies is a realistic and relevant difference.

Based on a power calculation using the Nquery Advisor software [25], 113 workers per group must be included for a difference of 15% (from 10% to 25%) with an alpha of 0.05 (two-tailed) and a power of (1-beta) = 0.80. A small cluster effect on the use of ergonomic measures at the level of the construction companies will be anticipated (ICC = 0.01). The construction companies have influence on the use of ergonomic measure by their employees, therefore there is a correlation between company and its employees. Since there is no interaction between the participating companies and because of the different characteristics of the companies (e.g. culture within the company, different trades) the assumption is that the correlation between the companies will be small. Based on the inclusion criteria, the assumption is made that the average number of construction workers (n) within a construction company is on average 25. This results in a cluster effect of 1.24 (1 + ((n-1) × ICC) and an adjusted sample size of 140 per group. To reach this sample size, we must include six construction companies per group.

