#### Process evaluation

With the exception of the behavioural change, each topic of the process evaluation will be reported descriptively on the company level and on the individual level. The items of the behavioural change will be pre-post tested using a General Linear Mixed Model. IBM SPSS Statistics 20 will be used for the statistical tests.

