## Discussion

The results of this study will help to gain insight into the effectiveness and possible barriers and facilitators of the two guidance strategies of a PE intervention on the use of ergonomic measures, work ability, physical functioning, limitations due to physical problems, process evaluation and economic evaluation. If shown to be effective in terms of an increase in the use of ergonomic measures, one or both strategies can be implemented by occupational health services to help construction companies or other companies with the implementation of ergonomic measures by means of an appropriate guidance strategy.

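### The outcome test named is change from baseline to six months, while the hypothesis, design and sample size concern the difference between the two guidance strategies

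*Protocol article*

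**What the plan says.** The question is set as a comparison of strategies in three places of the protocol article.

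- **Background:** face-to-face guidance is expected to improve use, work ability and physical functioning "while decreasing limitations due to physical problems more when compared to the e-guidance strategy".
- **Study design:** "The effectiveness of both guidance strategies will be compared on the use of ergonomic measures", followed by the other outcomes.
- **Sample size:** the calculation rests on "detecting a difference in the use of a new ergonomic measure between the face-to-face guidance strategy and the e-guidance strategy".

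The outcome test is set under Statistical analyses, Effect evaluation. To allow for workers being grouped in companies, the analyses of the outcomes "to test differences between baseline and after six months for both guidance strategies will be done using a Generalized Linear Mixed Model". That section names a test between the strategies only for the descriptive variables (t-test or Chi-square).

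Under Statistical analyses, Process evaluation, the wording is similar: "The items of the behavioural change will be pre-post tested using a General Linear Mixed Model". The Discussion draws the practical consequence: "If shown to be effective in terms of an increase in the use of ergonomic measures, one or both strategies can be implemented".

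**The concern.** The hypothesis and the sample size need a test of face-to-face against e-guidance. The sentence that defines the outcome analysis gives a different contrast, namely time. No strategy effect at six months, baseline-adjusted strategy effect or strategy-by-time interaction is named for any outcome. This is more than detail left to an analysis plan: a contrast is specified, and it is not the one the trial was designed around.

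Two things are at stake. First, a significant change in one arm and a non-significant change in the other is not evidence that the strategies differ, yet it is easily reported as such. Second, the Discussion sentence would let an increase within an arm count as effectiveness. Randomisation protects the comparison between arms; it does not protect a before-after change.

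**Working it through.** **1. Which contrast the sample size serves.** Inputs from Sample size: 10% and 25%, two-sided alpha 0.05, power 0.80, ICC 0.01, 25 workers per company.

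- Two-sample formula, no continuity correction: n = [1.96·√(2·0.175·0.825) + 0.842·√(0.09 + 0.1875)]² / 0.15² = 99.5, so 100 per group.
- With continuity correction: (99.5/4)·[1 + √(1 + 4/(99.5·0.15))]² = 112.5, so 113 per group, as stated.
- Design effect: 1 + 24·0.01 = 1.24, and 113·1.24 = 140.12, stated as 140.
- 140/25 = 5.6, so six companies (about 150 workers) per group, as stated.

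The article's figures therefore reproduce as a comparison between strategies. With 150 per group the effective size is 150/1.24 = 121, and a between-strategy test of 10% against 25% at six months has about 87% power (normal approximation, no continuity correction).

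**2. The passages side by side.**

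| Place | Contrast |
|---|---|
| Background, hypothesis | face-to-face vs e-guidance |
| Study design | face-to-face vs e-guidance |
| Sample size | face-to-face vs e-guidance |
| Effect evaluation, descriptive variables | face-to-face vs e-guidance |
| Effect evaluation, primary and secondary outcomes | baseline vs six months |
| Statistical analyses, Process evaluation, behavioural items | before vs after |

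**3. What follows if arms are judged by separate pre-post tests.** Let both arms have the same true change, and let each test have power w. Treating the arms as independent, P(exactly one significant) = 2w(1-w).

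| w | 0.3 | 0.5 | 0.8 | 0.9 | 0.96 |
|---|---|---|---|---|---|
| P | 42% | 50% | 32% | 18% | 8% |

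The maximum is 50%, at w = 0.5. At the upper end it falls below 5% once w exceeds (1 + √0.9)/2 = 0.974.

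**4. Where w might lie.** The article gives neither the expected within-arm change nor the correlation r between a worker's two answers, so both are assumed here. With 150 workers and design effect 1.24:

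SE² = [p0q0 + p1q1 - 2r√(p0q0·p1q1)]·1.24/150 and w = Φ((p1-p0)/SE - 1.96).

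| Common rise | r | SE | w | P(exactly one significant) |
|---|---|---|---|---|
| 10% to 17.5% | 0 | 0.044 | 0.40 | 48% |
| 10% to 17.5% | 0.3 | 0.037 | 0.53 | 50% |
| 10% to 17.5% | 0.5 | 0.032 | 0.66 | 45% |
| 10% to 25% | 0 | 0.048 | 0.88 | 21% |
| 10% to 25% | 0.3 | 0.041 | 0.96 | 8% |
| 10% to 25% | 0.5 | 0.035 | 0.99 | 2% |

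These rows are illustrations only. The 1.24 is a cross-sectional design effect. In a change within the same companies, stable company differences largely cancel and company-by-time variation takes their place. The 10% start is also borrowed: in Sample size it refers to newly introduced working methods, whereas the primary outcome counts use of ergonomic measures in four broad clusters over two months.

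**The case against.** The strongest reply is that the sentence is ambiguous. It mentions a single mixed model and does not say that each arm is tested separately or that the arms are ranked by their p-values. One model with strategy and time fits the words, Study design says that the strategies are to be compared, and an article may condense model terms. This stands in part. A reader might infer that the main question will go untested; the article does not support that, only that the contrast is not named in the sentence that defines the test. The contradiction remains, because the contrast that is named is another one, and the same section does name a between-strategy test when it means one.

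A reader might also infer that a false one-arm-only finding is always far more likely than 5%. The working does not support that: the figure runs from 2% to 50% over the cases shown.

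Two further arguments carry no weight here.

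- **No untreated arm.** The Limitations section acknowledges this and explains that interest lies in the guidance strategies. Regression to the mean from selective recruitment is possible, but only some recruitment routes select on known risk or an inspectorate warning. The Limitations explanation does, however, depend on the strategies being compared.
- **General versus Generalized.** Naming a General model for the behavioural items may be a slip of wording rather than a choice of a normal-theory model.

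The Discussion sentence is not an analysis rule, but it shows how a within-arm increase would be read.

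**Conclusion.** The point holds as a contradiction in the stated contrast, and the text is wrong as written. Three sections set a between-strategy question, the sample size reproduces only as a between-strategy calculation, and the outcome test is worded as baseline against six months. Read literally, the randomised comparison has no stated test.

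The size of the resulting error cannot be fixed from the article. If separate pre-post tests were used with equal true change, the chance of exactly one significant arm would be 2w(1-w), about 8% at w = 0.96 and at most 50%. This rests on independent arms, and on rises and within-worker correlations that the article does not give. The contradiction itself needs none of these assumptions.

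**What to change.** 1. In Effect evaluation, state the primary test as the between-strategy effect on six-month use, from a logistic mixed model with a random effect for company. Adjust for the worker's own baseline use where the two questionnaires can be linked.
2. If they cannot be linked, or a repeated-measures model is preferred, name the strategy-by-time interaction as the test and include company-by-time random effects.
3. Specify a small-sample correction, since there are only 12 companies.
4. Use the between-strategy contrast for the secondary outcomes too, and report within-arm change descriptively only.
5. Apply the same contrast to the behavioural items, with a link suited to categorical answers (several are yes/no, ability is good/poor, and knowledge has a third, don't-know answer).
6. Reword the Discussion so that the conclusion rests on the between-strategy contrast.

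The cost is a few sentences. Baseline use is already collected, so no new measurement is needed. The one practical condition is linkage of each worker's questionnaires, which the article does not describe; it should be confirmed before choosing between options 1 and 2.

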#### Primary

The use of ergonomic measures is the primary outcome measure and is defined as whether ergonomic measures are used during the last two months by the individual construction workers. The ergonomic measures are defined in four clusters: 1) mechanical measures for horizontal or vertical transportation, such as a crane, 2) ergonomic measures for raising equipment or materials, such as a raised mortar hod, 3) ergonomic measures to adjust working height on the worksite, and 4) ergonomic handtools. Construction workers will be asked at baseline and after six months whether they used ergonomic measures during the last two months during their work (yes or no). Examples of the ergonomic measures are adjusted for the different occupations.

In addition, construction workers are asked at the end of the intervention how many days they could and did use the implemented ergonomic measure during the previous 10 working days.

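### The outcome test is set on baseline-to-six-month differences, with no between-strategy contrast or baseline adjustment named, while the sample size powers a single-time comparison between strategies

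*Protocol article*

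**What the plan says.** Four places in the protocol article bear on this.

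- **Statistical analyses, Effect evaluation.** To allow for dependency within company, the outcome analyses to "test differences between baseline and after six months for both guidance strategies will be done using a Generalized Linear Mixed Model". No model terms are listed.
- **Sample size.** The trial is sized on "detecting a difference in the use of a new ergonomic measure between the face-to-face guidance strategy and the e-guidance strategy". The requirement is stated as "113 workers per group must be included for a difference of 15% (from 10% to 25" percent), "with an alpha of 0.05 (two-tailed) and a power of (1-beta) = 0.80". This is one proportion per group at one time.
- **Outcome measures, Primary.** The outcome is binary and asked twice: "Construction workers will be asked at baseline and after six months whether they used ergonomic measures during the last two months". The secondary outcomes are also measured at baseline and six months.
- **Background and Study design.** The hypothesis is a larger improvement under face-to-face guidance than under e-guidance, and the stated purpose is to compare the two strategies.

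**The concern.** The quantity that the analysis section tests is not the quantity that the sample size section powers. The analysis sentence has two natural readings.

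1. **A pre-post test within each strategy.** This gives two separate results and no test of one strategy against the other. One significant and one non-significant change would not show that the strategies differ.
2. **A difference between strategies in unadjusted change**, or equivalently an unconstrained time-by-strategy interaction. This adds the sampling error of the baseline answer to the comparison. If one group happens to start higher, part of that difference passes into the estimated effect through regression to the mean.

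At stake are whether the trial answers its own question and, under the second reading, how much power is given up when the baseline answer is already collected and could be used as a covariate.

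**Working it through.** **Inputs from the Sample size section.** Rates 10% and 25%; two-sided alpha 0.05; "a power of (1-beta) = 0.80"; ICC 0.01 ("A small cluster effect on the use of ergonomic measures at the level of the construction companies will be anticipated (ICC = 0.01"); 25 workers per company ("the average number of construction workers (n) within a construction company is on average 25"); six companies per group.

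**Inputs not in the documents, so assumed.** The correlation r between a worker's baseline and six-month answers, and baseline use p0. I take p0 = 10% in both groups and r from 0 to 0.5. A higher r is barely attainable: with 10% use at baseline and 25% at six months, the correlation of two yes/no answers cannot exceed √(0.10 × 0.75 / (0.90 × 0.25)) = 0.58. I apply the same design effect to every comparison.

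**The plan's own figure.** The two-proportion formula with continuity correction gives 113 per group (100 without). The design effect is 1 + 24 × 0.01 = 1.24, and 113 × 1.24 = 140. Then 140/25 = 5.6, so six companies. The plan's figures reproduce exactly, from a single-time comparison with no baseline term.

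**Six-month comparison.** The variance sum is 0.25 × 0.75 + 0.10 × 0.90 = 0.2775. With 140/1.24 = 113 effective workers per group, power without continuity correction is Φ(0.15/√(0.2775/113) − 1.96) = Φ(3.03 − 1.96) = 86%.

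**Unadjusted change.** Each group's variance is p1q1 + p0q0 − 2r√(p1q1 × p0q0). At r = 0.2:

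- face-to-face: 0.1875 + 0.09 − 0.4 × √(0.1875 × 0.09) = 0.2255
- e-guidance: 0.09 + 0.09 − 0.4 × 0.09 = 0.144
- sum 0.3695, which is 1.33 times 0.2775
- power: Φ(0.15/√(0.3695/113) − 1.96) = 75%

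**Baseline-adjusted.** The variance sum is 0.2775 × (1 − r²).

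| r | Variance ratio, change | Power, change | Variance ratio, adjusted | Power, adjusted |
|---|---|---|---|---|
| 0 | 1.65 | 65% | 1.00 | 86% |
| 0.2 | 1.33 | 75% | 0.96 | 87% |
| 0.3 | 1.17 | 80% | 0.91 | 89% |
| 0.4 | 1.02 | 85% | 0.84 | 91% |
| 0.5 | 0.86 | 90% | 0.75 | 94% |

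**Why adjustment is never worse here.** With equal variances, change has 2(1 − r) times the six-month variance and adjustment has (1 − r²) times. The gap is 2(1 − r) − (1 − r²) = (1 − r)², which is never negative.

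**Logit scale.** This is closer to a mixed model for a yes/no answer. At p0 = 10%, the time-by-strategy interaction has 47%, 55%, 67% and 75% power at r = 0, 0.2, 0.4 and 0.5, against 82% for the six-month comparison alone.

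**Low baseline use.** On the risk-difference scale the loss shrinks. At p0 = 2% and r = 0 the ratio is (0.2775 + 2 × 0.0196)/0.2775 = 1.14, and power is 81%. It does not shrink on the logit scale: at p0 = 5% the interaction has 33% power at r = 0.

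**Baseline imbalance.** With equal variances, a chance difference d moves the change estimate by about (1 − r)d and an unadjusted six-month comparison by about r·d. At r = 0.3 and d = 10 points these are 7 and 3 points, against a 15-point target. At p0 = 10% the standard deviation of d is √(2 × 0.09/113) = 4.0 points, so 10 points is 2.5 SD (two-sided probability about 1%). At p0 = 50% it is √(2 × 0.25/113) = 6.7 points, and the probability is about 13%.

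**The case against.** The strongest defence is that the analysis sentence never says change score. It lists no model terms, excludes no covariate, and comes from a journal article whose full analysis plan is not shown. A repeated-measures model with a common baseline mean would fit the sentence and behave much like baseline adjustment. This stands in part. A reader might infer that the plan commits to a change-score comparison, and the text does not go that far. But the sentence does name the tested quantity, and that quantity is not the one powered. This is more than a detail left to a later document.

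A reader might also infer that power certainly falls below 80%, for instance to 68% and 73% at r = 0.2 and 0.3 by scaling down from a nominal 80%. The documents do not support this. The 113 already contains a continuity correction, so the uncorrected starting point is 86% and the matching figures are 75% and 80%. Six full companies of 25 give 150/1.24 = 121 effective workers, and change then has about 77.5% and 82%. Above r of about 0.4, change is better than the six-month comparison that was powered.

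Nor do the documents show that a large baseline imbalance is likely. At the plan's ICC and an assumed 10% baseline, 10 points would be rare, and the Randomisation section pairs companies within occupation. The Limitations section concedes that pairing works only with an even number of companies per occupation. An unadjusted six-month comparison carries imbalance too, so the weakness is the absence of adjustment and not change alone.

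Finally, the sample size concerns a new measure, whose baseline use could be near zero; on the risk-difference scale the two approaches would then nearly coincide. The primary outcome, however, is defined as any use across four clusters, including cranes and hand tools, and is asked at baseline.

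**Conclusion.** The point holds as a mismatch that should be corrected. The analysis sentence fixes the test on the baseline-to-six-month difference without stating the between-strategy contrast that the hypothesis and sample size require. Under the within-strategy reading, the trial's question goes untested. Under the unadjusted-change reading, the cost on the risk-difference scale runs from about 21 percentage points of power at r = 0 (65% against 86%) to about 3 or 4 at r = 0.5 (90% against 94%), and it is larger on the logit scale. These sizes rest on an assumed 10% baseline, an assumed range of r, 113 effective workers per group and large-sample approximations. The direction does not depend on them: in this approximation baseline adjustment is never less precise than unadjusted change. Confidence is high that the sentence and the sample size do not match, and moderate that an unadjusted change comparison was intended.

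**What to change.** Replace the sentence in Effect evaluation so that the primary analysis is a generalized linear mixed model of the six-month answer, with strategy as fixed effect, the worker's own baseline answer as covariate and company as random effect. The equivalent repeated-measures model with baseline constrained to be equal across strategies would also serve; if that was the intention, say so. Use the same approach for work ability, physical functioning and limitations due to physical problems.

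Report the strategy effect also as an absolute difference with a 95% confidence interval, because the Sample size section defines relevance as 15 points absolute. Show changes within each strategy as description only.

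The cost is wording. No new data, workers or visits are needed, since the baseline answers are already collected. The one small downside is that workers without a baseline answer need a stated rule, such as a missing-baseline category or the constrained-baseline model.
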